24 genetically LP subjects with no GI symptoms in response to the ingestion of lactose (group 1).24 genetically lactase-non-persistent (LNP) subjects with no GI symptoms in response to the ingestion of lactose (group 2).72 genetically LNP subjects with GI symptoms in response to lactose ingestion (group 3).

Participants confirmed as genetically LP but experiencing GI symptoms after ingesting lactose will be excluded, as factors other than primary hypolactasia likely explain their symptoms.

The groups are chosen to allow discrimination of metabolic signals that relate to the genetic and clinical phenotypes of LI. Group 3 intentionally comprises more individuals to allow for secondary analysis of the differences in symptom severity, which is often very variable. The groups are important to enable the detection of biomarkers sensitive to differences in symptoms of LI to be captured.

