### Genetic and lactose tolerance screening

For all eligible participants, a home screening test will be conducted after consent is obtained. The home screening test kit will contain lactose powder and accompanying information so that the subjects can conduct a lactose tolerance test (according to the LHBT protocol) at their home. The test will be conducted based on a standardised, previously validated questionnaire,^17^ adapted to the most recent guidelines (https://www.esnm.eu/guidelines.html)^80^,^82^ that propose the use of 25 g of lactose for lactose tolerance testing. Briefly, abdominal pain, nausea, bloating, diarrhoea, borborygmi, as well as the sum of all symptoms, will be measured on a 10-point scale with symptom intensities ranging between 0 and 9. The home screening test kit will also provide material to collect a buccal sample to determine genetic polymorphisms commonly modulating LP.

From the participants who return the buccal samples and whose polymorphism for LP is measured, 120 participants will be selected and distributed into three groups based on their LP genetic profiles and symptomatic response to the ingestion of 25 g of lactose (lactose solution).

LP volunteers experiencing symptoms will be excluded as factors other than primary hypolactasia likely explain their symptoms.

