### Outcomes

#### Primary endpoints

The primary endpoint is the diagnostic performance of the Lactobreath profiles (the molecular breath profiles) for discriminating different clinical traits associated with LM after lactose intake. The choice of this endpoint allows an objective comparison with the current diagnostic measures used for LI diagnosis. It thus allows the novel test to be benchmarked against the current practice.

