The diagnostic performance of the lactose-induced breath profiles identified for the clinical traits will be assessed using the following parameters: sensitivity, specificity, positive predictive value, negative predictive value, the likelihood ratio of a positive test, likelihood ratio of a negative test as described by Beyerlein *et al*^17^ and Jellema *et al*.^81^ For each parameter, the novel breath profiles will be compared with the reference diagnostic tool. The participants are grouped by LHBT and genetic test results as these are commonly used in clinical practice for LI diagnosis and are, therefore, suitable for evaluating the performance of the breath biomarkers. The level of significance will be two-sided (α=0.05). Corrections for multiple testing will be made using the false discovery rate.^101^

Analysis populations: the analysis populations are defined by the criteria used to select the three study groups and the two assigned carbohydrate interventions, resulting in six groups for analysis.

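### The predictive values listed for the primary endpoint depend on recruitment quotas as well as on the test, so they hold only for this sample's mix

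*Protocol article*

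**What the plan says.** The Primary endpoints section under Outcomes defines the endpoint as the diagnostic performance of the breath profiles and says of this choice: "It thus allows the novel test to be benchmarked against the current practice". The Primary endpoint part of Statistical analysis lists the measures as "sensitivity, specificity, positive predictive value, negative predictive value, the likelihood ratio of a positive test, likelihood ratio of a negative test" and compares each with the reference tool. It gives no target prevalence, no re-weighting and no limit on how PPV and NPV are to be read.

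The sample is built by selection. Under Genetic and lactose tolerance screening: "From the participants who return the buccal samples and whose polymorphism for LP is measured, 120 participants will be selected". Study population and eligibility sets the groups at 24 lactase-persistent (LP) people without symptoms, 24 LNP people without symptoms and 72 LNP people with symptoms. It explains the unequal sizes: "Group 3 intentionally comprises more individuals to allow for secondary analysis of the differences in symptom severity". It leaves the fourth combination empty: "Participants confirmed as genetically LP but experiencing GI symptoms after ingesting lactose will be excluded".

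Under Intervention day, 20 people (4, 4 and 12 from the three groups) receive glucose and 100 receive lactose. The 20-person validation set is also stratified by group.

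**The concern.** Sensitivity and specificity condition on having or not having the trait. PPV and NPV condition on the test result, so they need a prevalence. When people are selected on the trait itself, that prevalence is a design choice. Here it was chosen to support a severity analysis and not to represent the people who would be tested.

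The predictive values are the figures a clinician is most likely to read as the chance that a tested person has, or does not have, the condition. Calculated directly from this sample and reported under the primary endpoint, they would invite that reading with nothing in the article to limit it.

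**Working it through.** **1. Quota shares (Study population and eligibility; Intervention day)**

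- All participants: 24 + 24 + 72 = 120. LNP (24 + 72)/120 = 80%; symptomatic at screening 72/120 = 60%.
- Lactose arm: 24 − 4, 24 − 4, 72 − 12 = 20, 20, 60, total 100. LNP 80/100 = 80%; symptomatic 60/100 = 60%.
- Validation set, if split proportionally as 4/4/12: LNP 16/20 = 80%; symptomatic 12/20 = 60%.

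The same prevalence therefore runs through modelling and validation.

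**2. Predictive values by prevalence**

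PPV = Se·p / [Se·p + (1 − Sp)(1 − p)]

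NPV = Sp(1 − p) / [Sp(1 − p) + (1 − Se)p]

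The article gives no expected sensitivity or specificity, so Se = Sp = 0.70, 0.80 and 0.90 are assumed. Its only prevalence figure is in the Introduction: about one-third of humans keep lactase activity, hence about two-thirds LNP. The 30% and 10% rows are assumptions.

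Example at Se = Sp = 0.80, p = 0.80: PPV = 0.64/(0.64 + 0.04) = 0.94; NPV = 0.16/(0.16 + 0.16) = 0.50.

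| Prevalence | PPV/NPV at 0.70 | PPV/NPV at 0.80 | PPV/NPV at 0.90 |
|---|---|---|---|
| 80% (LNP quota) | 0.90/0.37 | 0.94/0.50 | 0.97/0.69 |
| 67% (worldwide LNP) | 0.82/0.54 | 0.89/0.67 | 0.95/0.82 |
| 60% (symptom quota) | 0.78/0.61 | 0.86/0.73 | 0.93/0.86 |
| 30% (assumed) | 0.50/0.85 | 0.63/0.90 | 0.79/0.95 |
| 10% (assumed) | 0.21/0.95 | 0.31/0.97 | 0.50/0.99 |

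Within each column the likelihood ratios do not change: LR+ is 2.3, 4.0 and 9.0; LR− is 0.43, 0.25 and 0.11. An uninformative test (Se = Sp = 0.5) has a PPV equal to the prevalence: 0.80 for LNP and 0.60 for screening symptoms in this sample.

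**3. The genetic test as comparator, against screening symptoms**

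Count LNP as test-positive. Among those with symptoms, 72 are positive and 0 negative. Among those without, 24 are positive and 24 negative.

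- PPV = 72/96 = 75%; NPV = 24/24 = 100%.
- Sensitivity = 72/72 = 100%; specificity = 24/48 = 50%.

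All four are known before any breath is measured. The 100% figures follow from excluding symptomatic LP volunteers. They apply to screening status; symptoms on the test day may differ.

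**4. Comparison of two tests in the same people against the same standard**

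PPV odds = prior odds × LR+, and odds of disease after a negative test = prior odds × LR−. For given sensitivities and specificities, the order on PPV follows LR+ and the order on NPV follows LR− at any prevalence. The size of the gap does move. Take test A with Se 0.80 and Sp 0.80, and test B with Se 0.70 and Sp 0.90 (assumed):

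- p = 80%: PPV 0.941 v 0.966, gap 0.024; NPV 0.500 v 0.429, gap 0.071.
- p = 30%: PPV 0.632 v 0.750, gap 0.118; NPV 0.903 v 0.875, gap 0.028.

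**The case against.** The strongest reply has four parts.

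- **The comparison survives.** The aim is benchmarking, and step 4 shows that the ranking of two tests on PPV or NPV does not depend on the quotas. This stands. It protects the order, not the absolute values or the size of a difference.
- **The remedy is half in place.** Sensitivity, specificity and both likelihood ratios are in the same list, so a reader can derive predictive values at any prevalence, and a test that calls everyone positive would be exposed by a specificity of 0. This also stands, and it is why the correction is cheap. It does not make the raw values suitable as headline figures.
- **The scope is limited.** The quotas fix prevalence directly only for genotype and screening symptoms. The hydrogen breath test result, urinary metabolites and test-day symptoms are shaped by the quotas, but their prevalence is not set by them. This is correct.
- **The trial is a proof of concept, and an unseen analysis plan might add the caveat.** The Discussion does call for confirmation in other populations and in patients with other GI disorders. It does not address predictive values, and the choice of measures is stated in the article itself.

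A reader might infer that the predictive values describe the quotas and say nothing about the test, or that PPV must look high and NPV low whatever the profile. The documents do not support either. Both values depend on the test too, as the columns of the table show: at the 60% quota with Se = Sp = 0.90, NPV is 0.86. Nor are the raw values wrong for this sample; the error lies in carrying them to another setting.

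**Conclusion.** The concern holds in a limited form. Raw PPV and NPV from this design are valid only for the quota mix. For genotype at an assumed Se = Sp = 0.80, moving from the 80% quota to the article's own two-thirds LNP changes PPV/NPV from 0.94/0.50 to 0.89/0.67. Moving to an assumed 30% changes it to 0.63/0.90. The larger shift rests on that assumed prevalence, because the article names no target population figure. Against screening symptoms, the genetic test's predictive values are set by recruitment alone.

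It would go too far to conclude that the benchmark as a whole is invalid. Ranking is preserved, and measures that do not depend arithmetically on prevalence are already planned. The point is of moderate weight: it concerns how the primary results are estimated and presented, not whether the trial can answer its question.

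**What to change.** In the Primary endpoint part of Statistical analysis:

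1. Rest the performance claim and the comparison with the reference tool on sensitivity, specificity and likelihood ratios.
2. Report PPV and NPV only by Bayes' rule over a stated range of target prevalences. The genotype-by-symptom frequencies among people who completed both screening tests may be one point in that range. State that this is a volunteer pool, not a clinical population, and that its symptomatic LP members were excluded from the study, so the study has no test data for them.
3. Label any raw PPV or NPV as specific to this sample, and do not use tests of raw PPV or NPV differences as primary evidence.
4. Where the genetic test is compared against screening symptoms, state that its sensitivity and specificity are also fixed by the group sizes and the exclusion (step 3). Bayes' rule does not repair that.
5. Reconcile the description of the groups: this section says they are formed by hydrogen breath test and genetic result, while Study population and eligibility uses genotype and symptoms. The 80% and 60% figures follow from the latter.

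The cost is a change of wording, a few lines of analysis, and keeping counts from screening. No further participants or measurements are needed. The downside is that the reported PPV may look less favourable.

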The Lactobreath study will investigate lactose intolerance (LI) in a proof-of-concept study to demonstrate the potential of exhaled breath as a source of biomarkers associated with food intolerance. LI describes the clinical symptoms resulting from lactose malabsorption (LM), the failure to digest and/or absorb lactose in the small intestine. In infants, the disaccharide lactose that is present in milk is cleaved in the small intestine by lactase, an enzyme encoded by the *LCT* gene, to produce galactose and glucose. However, lactase expression is epigenetically regulated and decreases during infancy in most humans.^8^ Polymorphic modifications associated with the development of pastoral activities approximately 8000–9000 years ago counter the epigenetic regulation of LCT so that about one-third of the human population now maintains an intestinal lactase activity into adulthood.^9^ Recent research has revealed that epigenetic regulation of lactase expression also occurs in lactase-persistent (LP) adults, explaining the decreased lactose-digestive ability observed with ageing.^8 9^ The consumption of lactose in the absence of intestinal lactase activity results in the lactose entering the colon, fermented by the resident microbiota, producing short-chain fatty acids (SCFAs) and gases such as H_2_, CH_4_ and CO_2_. The osmotic changes resulting from lactose in the colon, combined with these fermentation end-products, induce GI symptoms of LI, abdominal pain, bloating, flatulence, nausea and diarrhoea.

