**Figure 2 F2:**
[figure not shown]
Overview of the planned intervention sampling protocol at the study site. EBC, exhaled breath condensate.

The urine samples will be used for metabolomics analysis and, in the case of female participants, for a pregnancy test. Participants with a positive pregnancy test will be excluded.

All measures are indicated with respect to the start of the test (ie, the start of the consumption of the assigned carbohydrate solution), defined as t_0_.

In addition, the participants will fill out the questionnaire on LI (as used for the screening survey) at time −30 and −10 min to describe symptoms of LI before the test (baseline symptoms).

Thirty minutes before the start of the test, participants will be instructed to affix two DigeHealth wearable devices around their abdomen to record bowel sounds: one in the upper left abdominal region and another in the lower right abdominal region.

The participants will be assigned to one of the two carbohydrate challenges using stratified randomisation based on the three groups defined by the pre-screening tests. The randomisation is defined using a web-based randomisation procedure, the Clinical Trial Randomization Tool provided by the National Cancer Institute’s Division of Cancer Prevention (https://ctrandomization.cancer.gov). 100 participants will be assigned to the lactose group and asked to ingest 25 g of lactose dissolved in 150 mL of water. The remaining 20 participants (4 participants from each group 1 and 2, and 12 participants from group 3) will be assigned to the glucose group and asked to ingest equimolar amounts of glucose (13 g)^83^ dissolved in 150 mL of water. The participants and investigators will be blinded during testing to the type of carbohydrate solution assigned. Measurement bias will be addressed for all analytical platforms by measuring the samples without removing the blinding.

For each participant, the carbohydrate solution must be consumed in a time lapse of 5 min. Following the solution intake, participants will be asked to rinse their mouths with a standard quantity of water (500 mL) to avoid the detection of solution-relevant residual molecules in the oral cavity.

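### For the symptom trait, the pooled specificity and likelihood ratios to be benchmarked against the reference tool are weighted by the 1:1 recruitment of symptom-free lactase-persistent and non-persistent people

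*Protocol article*

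**What the plan says.** Study population and eligibility sets three groups by quota:

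- First quota: "24 genetically LP subjects with no GI symptoms in response to the ingestion of lactose (group 1");
- Second quota: "24 genetically lactase-non-persistent (LNP) subjects with no GI symptoms in response to the ingestion of lactose (group 2");
- Third quota: "72 genetically LNP subjects with GI symptoms in response to lactose ingestion (group 3").

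It adds that "Participants confirmed as genetically LP but experiencing GI symptoms after ingesting lactose will be excluded". The classification rests on the home screening: under Genetic and lactose tolerance screening, "120 participants will be selected and distributed into three groups based on their LP genetic profiles and symptomatic response to the ingestion of 25 g" (the lactose dose at screening).

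Under Intervention day, "100 participants will be assigned to the lactose group" and 20 to glucose (4, 4 and 12 from groups 1, 2 and 3).

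Under Outcomes, the primary endpoint is diagnostic performance, chosen so that the new test can be benchmarked against current practice. Under Statistical analysis, Primary endpoint, the traits modelled are the hydrogen breath test response, genotype, urinary lactose metabolites and GI symptoms. Six accuracy parameters are listed, and then: "For each parameter, the novel breath profiles will be compared with the reference diagnostic tool". No reference tool is named for any trait. The section also says participants are grouped by hydrogen test and genetic results, whereas the eligibility section groups them by genotype and symptoms. Six analysis groups (three groups by two arms) are defined, but the accuracy parameters are not tied to them.

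**The concern.** Specificity and likelihood ratios are often treated as free of prevalence. That holds only if the people without the trait form one population. For symptoms they form two here, and existing tests should behave very differently in them. The Introduction says that lactose taken without intestinal lactase "results in the lactose entering the colon, fermented by the resident microbiota", with hydrogen among the products. A hydrogen test should therefore be negative in most LP people and positive in many symptom-free LNP people. The genetic test separates the two completely.

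A pooled specificity averages the two strata with the LP share as weight, and the recruiter sets that share. Adjusting predictive values to another prevalence does not remove this, because specificity already carries the mix. At stake is the stated purpose of the primary endpoint, since a reported advantage over current practice would partly reflect the recruitment ratio.

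**Working it through.** **Inputs from the document.** Quotas 24, 24 and 72; glucose arm 4, 4 and 12; symptomatic LP people excluded.

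**Reproducing the allocation.** (24 − 4) + (24 − 4) + (72 − 12) = 20 + 20 + 60 = 100, as stated for the lactose arm. The LP share of symptom-free lactose takers is w = 20/40 = 0.5.

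**Formula.** Pooled specificity for symptoms = w × Sp(LP) + (1 − w) × Sp(LNP).

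**Genetic test (no outside assumption).** Call LNP positive and use screening class. All 60 symptomatic people are LNP, and 20 of the 40 symptom-free people are LP.

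- Sensitivity 60/60 = 100%; specificity 20/40 = 50%; PPV 60/80 = 75%; NPV 20/20 = 100%; LR+ = 1/(1 − 0.5) = 2.0.
- Specificity equals w at any mix. At w = 0.8 it is 80% and LR+ = 1/(1 − 0.8) = 5.
- A profile with an assumed 70% specificity in both strata leads by 20 points at w = 0.5 and trails by 10 at w = 0.8.

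**Hydrogen test (assumption).** The document gives no hydrogen-positive rate in symptom-free people. Assume 90-100% of LP and 20-40% of symptom-free LNP people test negative, and compare with the same assumed 70%/70% profile. With a and b the hydrogen test's stratum specificities (LP, LNP), the crossover is w* = (0.70 − b)/(a − b).

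| Assumed negative, LP / LNP | Pooled at w = 0.5 | Profile minus hydrogen | Pooled at w = 0.8 | Profile minus hydrogen | w* |
|---|---|---|---|---|---|
| 90% / 20% | 55% | +15 | 76% | −6 | 0.50/0.70 = 71% |
| 90% / 40% | 65% | +5 | 80% | −10 | 0.30/0.50 = 60% |
| 100% / 20% | 60% | +10 | 84% | −14 | 0.50/0.80 = 62.5% |
| 100% / 40% | 70% | 0 | 88% | −18 | 0.30/0.60 = 50% |

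**A case without reversal.** Take a hydrogen test with 95% (LP) and 15% (LNP) and a profile with 95% and 60%. At w = 0.5 the values are 55% and 77.5%, a lead of 22.5 points. At w = 0.9 they are 87% and 91.5%, a lead of 4.5 points. The profile leads at both mixes, but the lead is five times larger at the trial's ratio.

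**Sensitivity.** By screening class every symptomatic participant is LNP, so sensitivity for symptoms does not depend on w. Sensitivity for LNP genotype does carry a quota: the 80 LNP lactose takers are 20 symptom-free and 60 symptomatic, giving weights of 25% and 75%.

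**Precision by stratum.** Exact 95% intervals: 14/20 = 70%, about 46-88%; 3/4 = 75%, about 19-99%. The second is what a hold-out of 20 would offer if split proportionally (4, 4 and 12).

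**The case against.** A reader might infer that the quota fixes the hydrogen test's specificity at some particular value near one half, or that it decides which test wins. The document supports neither. It gives a mechanism for hydrogen production, not the proportion of symptom-free people who exceed the 20 ppm cut-off; the assumed rates above already span 55-70%, and at one corner the two tests tie. Reversal also needs the profile to be more specific than the reference in LNP and less specific in LP (or the opposite). A profile at least as specific in both strata does not fall behind at any mix.

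Other objections have weight:

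- **The comparator is not stated.** The Introduction describes diagnosis of intolerance as hydrogen accompanied by symptoms. On that composite, symptom-free people are negative by definition and the averaging problem disappears, but the reference then contains the outcome. This is a reason to name the tool for each trait.
- **The scope is limited.** Specificity is one of six parameters, and symptoms are one of several traits, though they are the primary objective. This is not the whole primary comparison.
- **The 20:20 split is fixed at home screening.** If test-day symptoms define the trait, the split may differ, but the mix still comes from recruitment.
- **The plan partly anticipates this.** The groups were chosen to separate genetic from clinical phenotype, and six analysis groups are defined. However, each group holds a single screening symptom class, so likelihood ratios and predictive values require pooling across groups, and no weights are stated. The Discussion's proof-of-principle caveat concerns confirmation in other populations, not dependence on the quota.

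Layout of accuracy tables can be left to an analysis plan. The comparison itself and its stated suitability for benchmarking are already set out in the article.

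**Conclusion.** The concern holds in limited form. For symptoms by screening class, pooled specificity and the likelihood ratios built on it are quota-weighted averages, and the article plans to compare them with a reference tool without stratifying or reweighting. For the genetic test this is certain: 50% specificity and LR+ 2.0 follow from the quotas alone. For the hydrogen test the pull towards 50% follows from the mechanism, but its size is an assumption (55-70% at 1:1 over the ranges used). The size of any advantage of the breath profile depends on the recruitment ratio. Its sign may depend on it too: for an assumed profile at 70% in both strata, the crossover with the hydrogen test lies at an LP share of 50-71%. Sensitivity for symptoms is unaffected on this definition; sensitivity for LNP genotype is affected. The biomarker discovery work is not called into question, only how the benchmark is summarised.

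**What to change.** Amend the accuracy paragraph under Statistical analysis, Primary endpoint:

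1. Name the reference tool for each trait.
2. Report specificity for symptoms separately in symptom-free LP and symptom-free LNP people, with the paired difference from the reference in each.
3. Give any pooled specificity or likelihood ratio only over a stated range of LP shares, applied to both tests alike.
4. Do the same for sensitivity for LNP genotype, by groups 2 and 3.

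This changes wording only, because genotype and screening class are known for every participant. The price is precision. With out-of-sample predictions for the whole lactose arm there are 20 symptom-free people per stratum; in a proportional hold-out of 20 there are four, too few for a useful comparison. The stratum results should therefore be labelled descriptive.
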